## **2.3 Trial Design**

CCKO will utilize a wait-list variation of a randomized controlled trial design (**Figure 1**). The wait-list approach involves rolling out an intervention over time, whereby all participants are randomized into two groups (A and B) to receive the intervention at different time points determined at random (22,23). Group A would receive the intervention immediately (when resources become available; at time 0). Group B would be on the wait-list and receive the intervention after 12 months. This study design uses the time period before the intervention as the control period/baseline, to be compared in parallel to those receiving the intervention (22). Baseline measurements would be collected at month 0, and Groups A and B would be compared at months 6 and 12.

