### 3.3 Interventions

Patients will be randomized to receive either *usual care* for 1 year prior to their first clinic appointment (wait list group) or enrolled to be seen as soon as possible in a *complex care clinic* as part of the CCKO initiative. All eligible patients will be randomly assigned to wait list or the clinic prior to being approached for consent to participate in the evaluation of CCKO. The CCKO intervention involves intensive care coordination, defined as: “deliberate organization of patient care activities between two or more participants (including the patient) involved in a patient's care to facilitate the appropriate delivery of health care services. Organizing care involves the marshaling of personnel and other resources needed to carry out all required patient care activities and is often managed by the exchange of information among participants responsible for different aspects of care” (24). Within CCKO, intensive care coordination will specifically include: 1) the tailored, family/health care provider co-creation and regular updating of care coordination plans for each child which will be 2) facilitated and accounted for by key

workers partnering with families. The key worker would have a nursing or nurse practitioner background and will support providers in enacting the coordinated care plan between acute care, primary care, rehabilitation, home and community care. The key worker would be available to provide advice from Monday to Friday, 9 AM – 5 PM, and will also develop plans of care for emergencies after hours as part of care plan development. Resources to maintain intervention fidelity among key workers will be created and checked with oversight by PCMCH and the workers will connect annually in a meeting that will be co-attended by family representatives.

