### 3.7 Recruitment

At the Complex Care Clinic at each site, staff that have legitimate access to their health and contact information will identify and provide a study information letter to eligible patients using the CMC definition in **Figure 2**, who will further be contacted by the research assistant. An approximate 50% recruitment rate from a pool of N=400 (200/year) is conservatively estimated based on previous recruitment and current waitlists. Families who are inpatient or who are attending a clinic visit will be approached in person for consent. Families may also be sent an information package consisting of consent

and assent forms to participate. The research assistant will follow up if a response is not received, and only families that agree to participate would be contacted to set up a phone or in-person interview (based on the method most convenient for participants). Given the geographical distance, it is not feasible to conduct all of the recruitment in person. Every effort will be made to conduct recruitment in person at the Complex Care Clinic, however some recruitment will need to take place over the phone. In order to document consent instances over the telephone, there is a telephone consent form. The questionnaires would take place at baseline, 6 months, 12 months, and 24 months. Upon completion of each set of questionnaires families will be provided with a \$20 gift card to either Shoppers Drug Mart or Wal-Mart as a token of our appreciation for their time. Recruitment for the qualitative interviews would take place toward the end of the study, and a subsample of 25 families would be approached to answer questions about their overall experience with the Complex Care intervention.

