These scores will be used as three co-primary outcomes. The appropriate descriptive statistics will be used to compare groups with respect to baseline and demographic variables. Each outcome variable at Month 12 will be compared between groups using an ordinal regression incorporating center as a random intercept and adjusting for the baseline score. A two-sided test of hypothesis will be applied. The Holm-Bonferroni method will be used to deal with multiple testing (the three outcomes), where the overall target type I error rate is 0.05. The principle of intention-to-treat will be applied to the final analysis.

- iv) Child and Parent (Secondary) Outcomes: The data collection at 0 months and 6 months will be used to perform test-retest reliability, to establish baseline reference measures (0, 6, 12 months for this and other phases of intervention), and to assess for stability of outcome changes (24 months). Secondary child and parent outcomes will be compared at 0, 6 and 12 months using Bonferroni corrections to account for multiple testing. All secondary health system outcomes will be compared between the intervention and control as well.

- v) Process Outcomes: Process data collected through patient interviews will be first analyzed one participant at a time without making distinctions regarding the specific sample criteria articulated above. Following that, distinct issues brought forward for the specific sample criteria will be compared and contrasted to the main sample results. All interview data will be analyzed using a descriptive approach. The overarching themes will be selectively coded using the categories of ‘Active Ingredients’, ‘Fidelity’, ‘Dose’, and ‘Context’. The specific sub-themes under these pre-selected themes will be coded inductively.

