- vi) Health System Outcomes: A cost comparison analysis will be performed as part of the primary analysis. Additionally, cost-effectiveness will be subsequently performed, expressed as an incremental cost-effectiveness ratio (ICER), calculated by dividing the incremental costs of the intervention by the incremental difference in hospitalization days during the study period as the primary analysis and an ICER denominated on emergency department visits as a secondary analysis. Direct health care costs will include cost of the CCKO intervention and health services use by participants during the 12 month follow up period. Health services use by participants and covered by the provincial payer will be obtained through administrative data from the linkage with ICES. This will be expressed as absolute difference between the two groups with a 95% confidence interval. An interview administered expense diary will capture indirect costs, parent out-of-pocket expenses and additional health services covered by third-party payers. Intervention costs will include all Health Human Resources required to execute the intervention and will be allocated evenly across all participants. Extensive sensitivity analysis will be used to test the robustness of the results and explore uncertainty in any of the underlying assumptions. Probabilistic sensitivity analyses (PSAs) will also be used to establish the point estimate and 95% confidence interval for the ICERs obtained. The time horizon for the primary analysis will be one year, bounded by the date of randomization and the one year follow up interview.

Additional Analyses:

- i) All analyses will be extended to 24 months to assess for any outcomes that may have delays in change and to assess for ongoing effects in enrolled subjects. All primary and secondary analyses will be conducted for Year 2 of the study comparing outcomes among patients in the two groups that they were assigned to.
- ii) Comparison of PROMs and Interview Data: Qualitative interview data will be compared with PROMs to ascertain the association between experience-related themes and specific health outcome measures. Data on PROMs will be stratified based on scores for different outcomes, and compared with the qualitative data to gain a better understanding of how families' experiences with the intervention mapped on to patients' health-related outcomes.

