- iii) Sensitivity analysis #1: a) In order to address potential bias resulting from delays in initiation of complex care coordination after randomization, the primary analysis will be repeated using the initial complex care clinic visit date as the start of the intervention until 12 months from that date. b) To further explore this issue, an additional analysis will be performed through observation of the second year of outcome data post-randomization, using data from ICES. The comparison of Year 1 and Year 2 data will explore differences that may exist (in terms of group differences) and is expected to signal the importance of sensitivity analysis #1.
- iv) Sensitivity analysis #2: To account for health systems changes due to COVID-19 restrictions, which impacted most health service delivery across the country beginning March 13, 2020, an additional cost-effectiveness analysis will be conducted. For this analysis all health

service data collection will be truncated as of March 13, 2020 and the ICER will be calculated including health services use up to that date.

- v) Sensitivity analysis #3: Since health care utilization and costing data are being presented as per patient per year, in order to account for the small number of anticipated patients who may die or lose health insurance (OHIP) eligibility during the study, we will rerun the analyses excluding these patients. If this substantially changes study findings, data will be presented as per patient per month.

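### Sensitivity analysis #1 starts the clock at the first clinic visit, which wait-list children do not have in Year 1, so it gives no like-for-like comparison and part b cannot show that delay matters

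*Protocol*

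**What the plan says.** Section 3.12 sets the main analysis by assigned arm at a fixed time: "Each outcome variable at Month 12 will be compared between groups using an ordinal regression", and "The principle of intention-to-treat will be applied to the final analysis". Under Additional Analyses, sensitivity analysis #1a repeats the primary analysis "using the initial complex care clinic visit date as the start of the intervention until 12 months from that date". Part b then compares the group differences in Year 1 and Year 2 using ICES data and says that this "is expected to signal the importance of sensitivity analysis #1". Item i) of the same list adds a Year 2 repeat: "All primary and secondary analyses will be conducted for Year 2 of the study comparing outcomes among patients in the two groups".

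The design sections fix when each arm can have a first visit. Section 2.3 states: "Group B would be on the wait-list and receive the intervention after 12 months". Section 3.3 agrees: the wait-list arm has a year of usual care before its first appointment and is offered the clinic when that year ends. The intervention arm is seen at the soonest available appointment, and no expected delay is given.

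Section 3.7 fixes the survey schedule: "The questionnaires would take place at baseline, 6 months, 12 months, and 24 months". Section 3.4 counts these months from randomisation.

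**The concern.** The motive is sound. A child assigned to the clinic but first seen some months later has had less than a year of the intervention at Month 12. The remedy, however, ties time zero to an event that happens after randomisation and, in Year 1, in one arm only. No reference date is given for the other arm.

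This is the plan's named safeguard against delay bias, so its result is likely to be cited beside the main result as support. If it contrasts unlike windows, or two treated groups, agreement with the main result is not reassuring and disagreement cannot be interpreted. Part b adds a second risk: a change in the group difference that the planned crossover would produce anyway could be taken as a sign of delayed start.

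**Working it through.** The plan gives no figure for the delay, so there is none to reproduce. The check is calendar arithmetic.

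**Inputs**
- First visit in the intervention arm: month d after randomisation. The value of d is not in the protocol and is varied here as an assumption.
- First visit in the wait-list arm: month 12 + e, with e ≥ 0, because the clinic is offered after 12 months (sections 2.3 and 3.3). The value of e is also not given.
- FECC questionnaires: months 0, 6, 12 and 24 from randomisation (sections 3.4 and 3.7). The only 18-month time point, in section 3.4, is for the then-test on the KIDSCREEN and PROMIS measures, not FECC.

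**Step 1. Which windows does #1a compare?**
- *Both arms start at their own first visit.* The intervention window is month d to 12 + d. The wait-list window is month 12 + e to 24 + e. Both groups are under the intervention throughout, so there is no control. For e > 0 the wait-list window also ends after the last questionnaire at month 24.
- *Only the intervention arm is re-clocked.* The windows are d to 12 + d against 0 to 12. Events between randomisation and first visit are removed from one arm and kept in the other. A child assigned to the clinic who never attends has no start date. This is no longer a comparison of all randomised children from a common origin.
- *The control window is stretched to end at 12 + d.* The wait-list arm becomes eligible for the clinic at month 12, so up to d months of its window may be treated time. As a share of 12 months this is at most d/12: 1/12 = 8% for d = 1 and 4/12 = 33% for d = 4. These are upper bounds. If the wait-list arm waits equally long after month 12 (e = d), its first visit falls at month 12 + d and the treated share is about 0.

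**Step 2. Is there a FECC score at the target time?** The target is month 12 + d.

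| Assumed d (months) | Target month | Months after the Month 12 survey | Months before the Month 24 survey | Exposure at Month 12 (12 − d) | Exposure at Month 24 (24 − d) |
|---|---|---|---|---|---|
| 1 | 13 | 1 | 11 | 11 | 23 |
| 2 | 14 | 2 | 10 | 10 | 22 |
| 3 | 15 | 3 | 9 | 9 | 21 |
| 4 | 16 | 4 | 8 | 8 | 20 |
| 6 | 18 | 6 | 6 | 6 | 18 |
| 9 | 21 | 9 | 3 | 3 | 15 |

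A scheduled survey meets the target only when d = 0 or d = 12. Using the Month 12 survey instead simply gives the main analysis again. By the Month 24 survey the wait-list arm has already been offered the clinic.

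**Step 3. Which primary analysis is repeated?** Section 3.12 uses the term for the FECC comparison in item i). In item vi) it also uses it for the economic work, whose one-year horizon runs from randomisation. Step 2 applies on the first reading only. Step 1 applies on both, because re-windowing ICES records does not give the wait-list arm a Year 1 clinic date.

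**Step 4. Can part b detect delay?** Suppose the intervention works.
- No delay: there is a difference in Year 1, and it is expected to shrink in Year 2 as the wait-list arm is treated.
- With delay: there is a diluted difference in Year 1, and the same crossover follows in Year 2.

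The Year 1 to Year 2 change therefore mixes crossover with delay, and the comparison has no means of separating them.

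**The case against.** **The economic reading.** #1a may refer only to the economic analysis. Item vi) sets a boundary at randomisation, which is just what #1a moves. A 12-month window suits utilisation better than a single score, and part b and the next two sensitivity analyses concern ICES or cost data. This is a fair reading. It removes the questionnaire objection but not the unequal time zero.

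**Detail for the SAP.** The wait-list reference date and the handling of children never seen could be set in an SAP that is not shown. That would be enough if the protocol were silent. It states a start date, and the readings in Step 1 that follow from it all give unlike or treated windows. What is needed is a change to that rule.

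**Exploratory wording.** Part b says the comparison will explore differences, and the Year 2 analysis is by assigned group in a declared extension phase. That is right, and the Year 2 comparison by assigned arm is legitimate. Only the sentence linking it to the importance of #1 goes beyond what it can show.

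**Stronger readings that the document does not support.**
- A reader might infer that the trial's randomised comparison is broken. It is not: the Month 12 analysis stays by assigned arm.
- A reader might infer that #1a adds more bias than it removes. Neither bias can be sized without a delay.
- A reader might take 8% to 33% as the expected contamination. It is an upper bound on an assumed delay, under one of the three readings.
- A reader might infer that no untreated control exists after Month 12. Being offered the clinic is not being seen, so some untreated time may remain.

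**Conclusion.** The point holds for sensitivity analysis #1 and for nothing else in the plan. As written, #1a cannot give a comparison of the randomised arms over matching windows. This follows from the design logic for any delay above zero, on either meaning of primary analysis. On the FECC reading the required score is also not collected, unless the delay is exactly 0 or 12 months. Part b cannot distinguish a delayed start from the planned crossover.

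The direction and size of the added bias are not known. With a short delay both the mismatch and the need for the analysis are small. With a long delay both grow. The part b conclusion assumes only that the intervention has some effect and that wait-list children enter the clinic in Year 2 as planned. The change should be made, but the main result does not depend on it.

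**What to change.** Keep randomisation as time zero and keep every randomised child in the assigned arm.

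1. **ICES utilisation and cost.** Replace #1a with one lagged window applied identically to both arms, from day d to day 365 after randomisation. Fix d without reference to outcomes, for example from the distribution of delay to first visit in the intervention arm. A single constant applied to both arms keeps the groups comparable. Section 3.12 vii) refers to an analysis already done, so the record should show that d was set from visit dates alone.
2. **FECC.** Keep the Month 12 comparison by assigned arm, and report the delay to first visit and the number never seen. A complier estimate is optional. It needs stated assumptions: that assignment acts only through clinic exposure, that the form of any dose-response is right, and how an ordinal score is handled.
3. **Part b.** Delete the statement that the Year 1 versus Year 2 comparison will signal the importance of #1.
4. **Year 2.** Keep the comparison by assigned group and label it immediate versus 12-month-delayed start. A small Year 2 difference should not be read as loss of effect or as evidence of delay.
5. **Wording.** Say which primary analysis the sensitivity analysis accompanies.

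The cost is some wording and one re-run on existing data. The lagged window is shorter (11 months if d is 1 month, 8 months if d is 4), so its estimate is less precise. Children first seen after day d still contribute some untreated time.

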### 3.6 Sample Size

For the RCT, we conservatively project the total sample size to be 140 (70/arm) based on the following criteria: i) Two-sided test of the null hypothesis at the 5% level; ii) Power of 80%; iii) 10% lost-to-follow-up; projected smallest clinically important difference of 0.5 of the within-patient standard deviation, which is recommended by the developer as a moderate effect size (39).

The required sample size is considered feasible as it is estimated that a pool of about 250 patients are readily identifiable for recruitment at CCKO sites.

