### **3.8 Randomization – Sequence Generation, Allocation Concealment and Implementation**

CCKO randomization will be done using a computer-generated algorithm. Eligible children will receive the intervention in either Time 1 (approximately Jan 2017) or Time 2 (approximately Jan 2018). Randomization will be stratified by region/centre. Blocking will be used to ensure that the two comparison groups are about the same size throughout the trial for each site as well as for the trial as a whole. An allocation ratio of 1:1 with random block sizes between 6 and 8 will be used within each stratum (centre). This will help to ensure that clinicians or investigators will not decipher the block size. After patient consent is obtained, the study investigator or his/her delegate will assign the patient a unique identification (ID) number in sequential order that will be used throughout the study.

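### The reporting unit for utilisation and cost depends on the result of a sensitivity rerun, and the end of the one-year window is stated in two ways

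*Protocol*

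**What the plan says.** **Unit and exclusion.** Protocol section 3.12, Additional Analyses, item v (Sensitivity analysis #3) starts from results given per patient per year. It expects a small number of children to die or lose OHIP eligibility and states no rate. It then says "we will rerun the analyses excluding these patients. If this substantially changes study findings, data will be presented as per patient per month".

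**Window.** Section 3.12, Primary Analyses, item vi (Health System Outcomes) says "The time horizon for the primary analysis will be one year, bounded by the date of randomization and the one year follow up interview". The same item also counts health services use over a 12-month follow-up, and section 3.4 (Health System Outcomes) gives a 12-month horizon. Use covered by the provincial payer comes from ICES linkage; the interview supplies the expense diary.

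**Weight of these results.** Item vi makes the cost comparison part of the primary analysis. It takes the difference in hospitalisation days as the main denominator of the ICER.

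**Analysis principle.** Section 3.12, item iii, says "The principle of intention-to-treat will be applied to the final analysis".

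**The concern.** Two stated rules are at issue.

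First, the rule for choosing the unit looks at the result. A rerun is made, someone judges whether the findings changed enough, and that judgement decides which figures are presented. No threshold is given. The rerun that drives the decision drops children because of events after randomisation, so it is itself a selected comparison. The rule also does not say whether the monthly figure is total use over total person-months or an average of each child's own rate, or whether the excluded children come back into it. A reader of the results could not tell a planned unit from a chosen one.

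Second, a window that closes at an interview has no fixed length. It has no end at all for a family without a 12-month interview, and section 3.12, Additional Analyses, item vii reports that missing outcome data were extensive. Linked utilisation data do not need an interview, so nothing is gained by tying the two together.

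At stake are the cost comparison, the hospital-day contrast and the ICER.

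**Working it through.** **1. The plan's own figure, to settle scope.** Section 3.6 gives "Two-sided test of the null hypothesis at the 5% level", power of 80%, "projected smallest clinically important difference of 0.5 of the within-patient standard deviation" and "10% lost-to-follow-up".

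- Per arm: 2 x (1.960 + 0.842)^2 / 0.5^2 = 62.8, so 63.
- With 10% loss: 63 / 0.9 = 70 per arm, 140 in total.

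This matches the protocol's 140. Nothing in the present point enters that calculation.

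**2. Does the choice of unit matter?** If every child has 12 months of data, dividing by 12 is cosmetic. The switch matters only through children with shortened person-time, which are the children in question.

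The protocol gives no death rate or use figures, so these are assumptions:

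- survivors use 10 hospital days a year in both arms;
- children who die do so at month 6, after m = 20 or 40 days of use;
- deaths are 3% in the intervention arm and 6% in the wait-list arm.

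Formulas for an arm with death proportion p:

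- All randomised, per patient-year: (1 - p) x 10 + p x m
- Excluding deaths: 10
- Pooled rate x 12: [(1 - p) x 10 + p x m] / [(1 - p) x 12 + p x 6] x 12
- Mean of individual rates x 12: (1 - p) x 10 + p x (m / 6) x 12

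Worked for m = 20:

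- All randomised: 9.7 + 0.6 = 10.3 against 9.4 + 1.2 = 10.6, difference -0.30.
- Pooled: 10.3 / 11.82 x 12 = 10.46 against 10.6 / 11.64 x 12 = 10.93, difference -0.47.
- Mean of individual rates: 9.7 + 1.2 = 10.9 against 9.4 + 2.4 = 11.8, difference -0.90.

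| Intervention minus wait-list, days per year | m = 20 | m = 40 |
|---|---|---|
| All randomised, per patient-year | -0.30 | -0.90 |
| Excluding deaths | 0 | 0 |
| Pooled person-month rate x 12 | -0.47 | -1.10 |
| Mean of individual monthly rates x 12 | -0.90 | -2.10 |

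With 3% deaths in both arms, every row is 0. With the proportions reversed (6% and 3%), the signs reverse.

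So, under these assumptions, the exclusion can remove a difference that the full comparison shows. The two readings of a monthly figure differ about twofold (0.90 / 0.47 and 2.10 / 1.10, both 1.9). The measures also answer different questions: the annual total counts a child's use after death as zero, while a monthly rate describes use while alive.

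**3. Does the end of the window matter?** Suppose both arms use services at the same rate and the interview falls later in one arm by 0.5, 1 or 2 months. That arm's 12-month total rises by 0.5/12 = 4.2%, 1/12 = 8.3% or 2/12 = 16.7%. On 10 days a year this is 0.42, 0.83 or 1.67 days. With equal timing the effect is 0. The protocol gives no interview dates by arm.

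**The case against.** The strongest reply is that the main analysis is sound. A reader might infer that children who die or lose coverage are dropped from it and that intention-to-treat is breached. The documents do not support that: the exclusion is a labelled sensitivity rerun, and no text removes these children from the main cost or hospital-day comparison. This part of the reply stands in full.

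A reader might also infer that the window certainly varies by family and arm. The sentence that mentions the interview also says one year, and 12 months appears elsewhere. The interview may be named only because it supplies the expense diary. Nothing says that ICES extraction stops early or is lost when an interview is late or missed. This too stands: a variable window is one reading, and the defect is an ambiguity.

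Nor do the documents show that ICES observes every linked child for a full 365 days, which would fail after loss of OHIP.

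It can further be said that the person-time method and the threshold belong in a statistical analysis plan, which is not at hand. That holds for the method as an omission. It does not rescue the switch, which the protocol itself states and which would still let the result choose the unit even with a threshold.

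**Conclusion.** The point holds in limited form. The protocol contains a results-driven switch of the presented unit, without a threshold, triggered by a rerun that selects on post-randomisation events. It also describes the end of the utilisation window in two ways, one of which could make person-time depend on interview timing.

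The size of any bias is unknown. It requires the arms to differ in deaths, coverage loss or interview timing, and the documents give no rates for any of these. The illustrative figures show only that the choice of unit can matter; it would be wrong to quote any of them as the bias in this trial.

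The consequences are confined to the cost comparison, the hospital-day contrast and the ICER. The three FECC co-primary outcomes and the sample size are untouched. The change is worth making because these results are prominent and the correction is nearly free.

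**What to change.** In section 3.12, Primary Analyses, item vi, set the ICES utilisation window at 365 days from randomisation for every randomised linked child, whatever the interview date, and align section 3.4 with it. The interview can remain the source of the expense diary.

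In Additional Analyses, item v:

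- Keep all such children in the main per-patient-year analysis. Count use after death as zero. Treat time after OHIP loss as censored, not as zero use, and state how the annual figure allows for it.
- Always report one pre-defined person-time analysis beside it: total use over total person-months, or a model with a log person-time offset.
- Tabulate deaths and OHIP losses by arm.
- Delete the clause that changes the unit when findings change. The exclusion rerun may stay as a labelled sensitivity result that triggers nothing.

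The cost is a change of analysis wording. It needs no further children, visits or data sources beyond the linkage already planned.
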